# Effect of biodegradable microneedle acupuncture for symptom relief moderate or milder atopic dermatitis: a study protocol for a multicenter, randomized, sham-controlled trial

**DOI:** 10.1186/s12906-026-05330-5

**Published:** 2026-03-09

**Keywords:** Atopic dermatitis, Biodegradable Microneedle Acupuncture, Randomized controlled trial, Sham, Economics, Study protocol

## Abstract

**Background:**

Atopic dermatitis (AD) has no definitive cure; therefore, alternative treatments should be developed. We have demonstrated in preliminary clinical trials that Biodegradable Microneedle Acupuncture (BMA) treatment improves symptoms and is safe for mild to moderate AD.

**Aims:**

The study focused on evaluating the effectiveness and safety of a new medical device called BMA for AD, while also assessing its cost-effectiveness. It also explored the gut microbiome of patients with AD before and after BMA treatment.

**Methods:**

This multicenter, participant-assessor-blinded, sham-controlled trial will be conducted from January 10, 2025, to January 10, 2026. In total, 184 participants with AD (*n* = 92 per group) will be recruited. Participants will be assigned randomly to two equal-sized groups: the BMA and sham groups. Treatment will be administered three times per weekduring the 4-week intervention phase.

The primary outcome measure will be the objective SCORing Atopic Dermatitis index. Secondary outcome measures will include the Eczema Area and Severity Index, Dermatology Life Quality Index, Patient-Oriented Eczema Measure, and pruritus Visual Analog Scale scores.

Other outcome measures will include gut microbiome, economic and safety evaluations.

**Discussion:**

This study protocol will provide an important and thorough assessment of the effectiveness of BMA treatment in improving the symptoms of moderate or milder AD. In addition, we will evaluate the safety and costeffectiveness of BMA. We will also determine the link between AD and the microbiome.

This clinical trial has been registered with the Korean Clinical Trial Registry (registration number: KCT0009870; date of registration: 25 October 2024).

## Background

Atopic dermatitis (AD) is a chronic inflammatory dermatitis prone to flare-ups, with an increasing incidence in recent years [1]. It is a skin disease that significantly reduces the quality of life of patients and their families, but it remains difficult to treat due to the lack of a definitive cure and the side effects and high costs associated with treatment [1–3].

Currently, there is no definitive conventional cure for AD; therefore, the use of complementary and alternative therapies, such as acupuncture, is increasing [4].

Acupuncture has been shown to alleviate type 1 hypersensitivity-induced itchingin patients with AD [5] and has been reported to improve AD by blocking 5-HT receptors, thereby reducing histamine-induced acute itching [6, 7]. Acupuncture also relieves pruritus in AD by decreasing serum IL-2 and IL-4 levels while increasing interferon-γ levels in patients with chronic eczema [6]. Randomized controlled trials (RCTs) have already been conducted in AD patients to assess symptom changes following acupuncture treatment and to compare its effectiveness with sham acupuncture [8].

Biodegradable microneedle acupuncture (BMA) is an innovative medical device designed to overcome the limitations of traditional intradermal acupuncture (IDA). IDA is a form of acupuncture intended to provide prolonged stimulation by attaching a thumbtack-shaped needle to an acupointand applying continuous stimulation for a day to a week. However, long-term use of IDA can cause side effects such as foreign body sensation, oozing, and itching, particularly in individuals allergic to metal. To eliminate these adverse effects, we developed BMA using biodegradable hyaluronic acid, which has been demonstrated to be both safe and effective.

According to data from our unpublished preliminary clinical trial, we confirmedthe efficacy and safety of BMA treatment in AD. Our data indicate that BMA treatment is effective and safe in ameliorating AD symptoms.

This trial will provide a research framework to evaluate the clinical efficacy, safety, and cost-effectiveness of BMA in the treatment of patients with moderate or milder AD. We also hope that Korean medicine, including acupuncture, will play a greater rolein the management and treatment of AD.

## Methods

### Study setting

This multicenter, participant-assessor-blinded, sham-controlled trial will be conducted at two hospitals affiliated with Dongshin University: Naju Dongshin University Korean Medicine Hospital and Dongshin University Mokpo Korean Medicine Hospital, Korea. The trial has been registered with theregistered with the Clinical Research Information Service of the Republic of Korea (registration no. KCT0009870).

At the time of writing this report, enrollmenthas not started. Participant recruitment will take place from January 10, 2025, to January 10, 2026.

The present protocol satisfied the Declaration of Helsinki and was conducted following CONSORT reporting guidelines [9]. Written informed consent was obtained from each participant before registration. A flowchart of the study is shown in Fig. 1.

**Fig. 1 Fig1:**
[figure not shown]
CONSORT flow diagram of the study design. This flow diagram illustrates the sequence of participant enrollment, randomization, allocation, follow-up, and analysis in the multicenter, randomized, sham-controlled trial aimed at assessing the efficacy and safety of Biodegradable Microneedle Acupuncture (BMA) for individuals with moderate or milder Atopic Dermatitis (AD). A total of 184 participants will be divided into two groups: the BMA group (*n* = 92) and the Sham BMA group (*n* = 92). Participants will be evaluated at baseline and again at weeks 5 and 8. The diagram also presents the exclusion criteria, instances of loss to follow-up, and the stages of final analysis

This flow diagram illustrates the sequence of participant enrollment, randomization, allocation, follow-up, and analysis in the multicenter, randomized, sham-controlled trial aimed at assessing the efficacy and safety of Biodegradable Microneedle Acupuncture (BMA) for individuals with moderate or milder Atopic Dermatitis (AD). A total of 184 participants will be divided into two groups: the BMA group (*n* = 92) and the Sham BMA group (*n* = 92). Participants will be evaluated at baseline and again at weeks 5 and 8. The diagram also presents the exclusion criteria, instances of loss to follow-up, and the stages of final analysis.

### Eligibility criteria

#### Inclusion criteria

Patients meeting all the following criteria will be enrolled in this study:

Male or female patients aged 19–70 years at the screening visit.Diagnosis of AD according to the Hanifin and Rajka criteria (> 3 of 4 major symptoms and > 3 of 23 minor symptoms).Patients scored 10–40 in the O-SCORAD index.Patients who can read and write Korean and who voluntarily submitted written consent with their signature.

#### Exclusion criteria

Patients meeting any of the following criteria will be excluded:

Patients with severe skin diseases other than AD or severe oozing and maceration of the atopic lesions, who may affect the results of this study in the investigators’ opinion.Patients with skin diseases due to other internal (e.g., liver diseases, renal failure), psychotic, or neurological conditions that are expected to affect the results of this study.Patients who have used systemic medications, including corticosteroids, antibiotics, immunosuppressants/immunomodulators (systemic corticosteroids, cyclosporine, mycophenolate mofetil, interferon-gamma) within 1 month before the screening visit. Exceptionally, the administration of systemic antihistamines was allowed during the trial within the dose at the randomization visit if they had been administered at a constant dose for 1 month before randomization. Reduction and discontinuation were permitted, but an increase was prohibited.Other severe comorbidities (e.g., heart diseases, kidney diseases, liver diseases, respiratory diseases, malignancy, immunodeficiency, etc.) deemed inadequate by the principal investigator. The abnormality criteria for liver function is defined as aspartate transaminase (AST) or alanine transaminase (ALT) level five times higher than the upper limit of the analyzed institution, and those for renal function is defined as three times higher than the upper limit of the analyzed institution.Severe or uncontrolled asthma (exacerbation of asthma requiring systemic corticosteroids for at least attacks of 3 days more than two times per year)Allergy to adhesives.Pregnant, lactating women, or women planning pregnancy.Patients deemed unsuitable by the principal investigator.

#### Dropout exclusion criteria

Each participant’s completion status will be monitored. In case of discontinuation, the reason for the discontinuation will be recorded. Cases in which the trial can be discontinued are as follows: 

The investigators discover that the participant does not meet the inclusion or exclusion criteria.The participant experiences any serious adverse events (AEs) or adverse events that make continuation in the trial challenging.The participant or legal representative requests to discontinue the trial owing to unsatisfactory therapeutic effects.The compliance of each participant is < 80%.The investigators or participants violate the study protocol.The participant withdraws consent to participate in the trial.The participant is lost to follow-up.The participant receives any treatment that may affect the study results without the investigator’s approval.Participants deemed incapable of continuing the trial by the investigators.

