**Fig. 4 Fig4:**
[figure not shown]
Locations of acupoints for biodegradable microneedle acupuncture (BMA) Treatment This figure depicts the five acupoints utilized in the study for BMA treatment. The chosen acupoints are LI11 (Quchi), LI4 (Hegu), PC6 (Neiguan), ST36 (Zusanli), and SP10 (Xuehai). These points are strategically positioned on the arms and legs and are frequently employed in traditional Korean medicine to manage inflammation, modulate the immune system, and treat skin-related issues. The application of BMA at these specific points is intended to amplify the therapeutic effects for symptoms associated with atopic dermatitis (AD)

For 4 weeks, treatments will be performed three times a week for a total of 12 times.

The investigators will instruct the participants on how to remove the BMA and disinfect the treated area themselves 4 h after treatment. The investigators will distribute Medical Device Removal Time record diaries to the participants at each visit and instruct them on the removal time record sheets.

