#### General principles

The safety and full analysis sets (FAS) of this trial will include all the participants who received any intervention at least once after randomization. The per-protocol set will only include participants in the FAS who completed the entire trial without protocol violations. The FAS is primarily used for outcome analysis, although additional outcome analyses of the per-protocol set may be performed. The safety set will be used for safety assessments, including the primary outcome of the trial. Missing values will be handled using the last observation carried-forward method.

Statistical analyses will be performed using SAS (SAS Institute Inc., Cary, NC, USA) or SPSS (IBM Corp., Armonk, NY, USA) softwares for Windows. Statistical significance is set at *p* < 0.025 for a one-tailed test and *p* < 0.05 for a two-tailed test.

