#### Economic outcomes analysis

The QALYs will be calculated using the Area Under the Curve (AUC) method. Treatment costs will be estimated by combining the frequency of each treatment and their unit costs. The economic evaluation will primarily follow the Intention-to-Treat (ITT) principle, which includes all randomized participants, regardless of adherence to the treatment protocol, to assess the effectiveness of the treatments. A secondary analysis will be performed based on the Per-Protocol (PP) principle to evaluate the sensitivity of results to missing data. For missing data in the ITT analysis, the missing data mechanism will be primarily examined using missing diagnosis method, and appropriate imputation method will be applied for building up ITT data before proceeding the analysis. The analysis period will be 8 weeks (the total follow-up period). If additional extrapolation is required, regression models or decision analysis models will be used to estimate costs and effects beyond the follow-up period. After the clinical trial period, the total analysis duration will use the 2024 South Korean currency (KRW) for cost calculations, and a 5% discount rate will be applied, in accordance with the Health Insurance Review and Assessment Service (HIRA) guidelines for cost-effectiveness evaluations. The analysis will be conducted from a societal perspective. In the base-case analysis, representative values (such as mean values) for parameters will be used, while probabilistic sensitivity analysis will be performed using all possible distributions and representative values for the estimated parameters. The results will be presented in tables, including Incremental Cost-Effectiveness Ratios (ICER), Cost-Effectiveness Planes (CEP), Cost-Effectiveness Acceptability Curves (CEAC), and Information Curve values. Statistical analysis for the economic evaluation will be conducted using Stata (MP 16.1) and R (4.3.2), and modeling for extrapolation will be performed using TreeAge Pro(Healthcare version 2023).

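### Trial participation, not only study treatment, can be discontinued for non-adherence or violations, and the text shown seeks no Visit 13 outcome afterwards from participants who stay in the FAS and ITT sets

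*Protocol article*

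**What the plan says.** The section Dropout exclusion criteria introduces its list with "Cases in which the trial can be discontinued are as follows". What can be discontinued is the trial. The list includes:

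- compliance below 80%;
- "The investigators or participants violate the study protocol";
- ineligibility discovered after entry;
- treatment received without the investigator's approval;
- the case where the participant or legal representative "requests to discontinue the trial owing to unsatisfactory therapeutic effects".

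These stand beside serious or limiting adverse events, withdrawn consent, loss to follow-up and the investigator's judgement that the participant cannot continue. No distinction is drawn between ending study treatment and ending follow-up.

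Under General principles the full analysis set (FAS) is everyone treated at least once after randomisation. "The FAS is primarily used for outcome analysis", and missing values are filled by last observation carried forward (LOCF). The per-protocol set is the part of the FAS that completed without violations. The Economic outcomes analysis rests on an ITT set "which includes all randomized participants, regardless of adherence to the treatment protocol".

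Primary outcome measure places O-SCORAD at screening, Visit 1 and Visit 13. Secondary outcome measure places the other scales at Visits 1 and 13. Sample size plans for 30% dropout.

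**The concern.** The analysis sets and the discontinuation list pull in opposite directions. The FAS and ITT sets exist so that adherence and violations after randomisation do not decide whose outcome counts. The discontinuation list lets those same events end a participant's time in the trial before the one visit at which the outcome is measured. Such a participant stays in the denominator with no observed result, and LOCF supplies the baseline value in its place.

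Two things are at stake. Zero-change scores shrink the difference between arms and widen the spread, which costs power. If the arms lose different proportions, the comparison is also biased. Unequal loss is plausible: the Blinding section says the treating doctor cannot be blinded, and adherence may depend on what the participant experiences. The loss cannot be repaired later, because a Visit 13 assessment that was never made cannot be recovered in the analysis.

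**Working it through.** **1. The plan's own figure.** Sample size gives 64 per group before dropout and 30% dropout: 64 / (1 − 0.30) = 91.4, rounded up to 92. This reproduces. The power and SD behind the 64 are not stated. A difference of 2.0 with SD 4 and 80% power (both assumed) gives 2 × (1.96 + 0.84)² × 4² / 2² = 63 by the normal approximation and 64 by the t-test, so 64 is reachable. A 30% loss leaves 92 × 0.70 = 64.4 observed per group. The inflation therefore protects power for an analysis of observed cases: with 64 per group, 84% at the pooled pilot SD of 3.82 or 81% at SD 4. That is not the stated main analysis, which is the FAS with LOCF.

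**2. Score of a participant discontinued before Visit 13.** The last O-SCORAD is Visit 1, so change = Visit 1 − Visit 1 = 0.

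**3. Equal loss in both arms.** The inputs are the pilot changes in Sample size, 9.2 (SD 3.73) and 7.2 (SD 3.91), with the pilot IDA value standing in for sham (assumption); 92 per arm; two-sided 5%; loss d unrelated to outcome. In each arm:

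- mean = (1 − d) × μ
- variance = (1 − d) × SD² + d × (1 − d) × μ²
- power = Φ(difference / (SD × √(2/92)) − 1.96), with SD the root of the average of the two variances

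For d = 0.30:

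- BMA variance = 0.7 × 3.73² + 0.21 × 9.2² = 27.5
- sham variance = 0.7 × 3.91² + 0.21 × 7.2² = 21.6
- SD = √24.55 = 4.95
- difference = 0.7 × 2.0 = 1.4
- standard error = 4.95 × √(2/92) = 0.731
- 1.4 / 0.731 = 1.92, so power = 48%

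| Loss per arm | Difference | SD | Power |
|---|---|---|---|
| 0% | 2.0 | 3.82 | 94% |
| 10% | 1.8 | 4.39 | 79% |
| 15% | 1.7 | 4.59 | 71% |
| 20% | 1.6 | 4.75 | 63% |
| 30% | 1.4 | 4.95 | 48% |

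With SD 4 in both arms the end rows become 92% and 47%.

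**4. Unequal loss with no true difference.** Take a change of 7.2 in both arms and the pilot SDs. The spurious difference is 7.2 × (difference in loss).

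- 25% versus 35%: 7.2 × 0.10 = 0.72; SD 4.58; standard error 0.675; ratio 1.07; two-sided rejection about 19%.
- 20% versus 40%: 7.2 × 0.20 = 1.44; SD 4.53; standard error 0.668; ratio 2.16; rejection about 58%.

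The bias favours the arm with less loss.

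**5. Dilution.** The 94% row gives participants who stop treatment the full effect. Suppose instead that 30% stop, all are measured at Visit 13, and they keep a fraction r of the effect. The difference is then 2.0 × (0.7 + 0.3r). With SD held at 3.82 and standard error 3.82 × √(2/92) = 0.563:

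- r = 0.5: 1.7 / 0.563 = 3.02, power about 86%
- r = 0: 1.4 / 0.563 = 2.49, power about 70%

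Even with no retained effect, observed values do better than zero-change scores at the same 30% (48%), because the spread is not inflated.

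**The case against.** Several points on the other side have force.

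- **The wording is permissive.** The text says the trial can be discontinued. A reader might infer that everyone below 80% compliance, or with any violation, is removed automatically; the document does not say so. Discretion does not remove the problem, though, because it adds a judgement after randomisation about who leaves.
- **Poor effect counts only on request.** A reader might infer that poor response itself ends participation. The listed ground is that the participant or legal representative asks to leave, which any trial must honour. That loss is not created by the plan, although such a person could still be asked to attend Visit 13.
- **The article is condensed.** The full protocol may provide an early-termination or continued Visit 13 assessment, and the schedule figure is not shown. Loss of Visit 13 is therefore inferred from a list that speaks of the trial and from the absence of any follow-up provision in the text shown.
- **Other assessments are mentioned.** The Fig. 1 legend refers to weeks 5 and 8, and Treatment phase speaks of checks during therapy. If an O-SCORAD were taken between Visits 1 and 13, LOCF would carry that value instead. The outcome sections name only the visits given above, and someone out of the trial would miss a week 8 visit as well.
- **Compliance is not defined.** The plan states that "treatments will be performed three times a week for a total of 12 times". If compliance meant attendance, fewer than 80% would be 9 sessions or fewer (9/12 = 75%, 10/12 = 83%). With independent misses at 5%, 10% or 15% per session, 2%, 11% or 26% of participants would meet it. Neither the definition nor the miss rates come from the document, so this range does not size the problem. The text also does not say how much of the planned 30% comes from these grounds.
- **The FAS does not become a per-protocol analysis.** That inference is tempting but wrong. Participants scored as zero change stay in the FAS and pull the estimate; a per-protocol analysis leaves them out.
- **A completer comparison overstates the gain.** Recovering half of the 30% raises observed cases from 64 to 78 per arm and t-test power from 84% to 90%, but only if the 14 recovered participants per arm show the full effect. Power is 84% if they keep half and 76% if they keep none, so on that comparison there is no gain at or below half. It is also not the analysis the plan names.

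**Conclusion.** The point holds as a gap between the discontinuation list and the analysis sets. Participants discontinued for low compliance, a violation, late-found ineligibility or unapproved treatment remain in the ITT set and, once treated, in the FAS. Followed as written, the text yields no post-treatment outcome for those who leave before Visit 13 and scores them as unchanged. Non-compliance and violations need not end participation for analytic reasons, since the per-protocol set already deals with violations at the analysis stage.

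Under the stated FAS with LOCF, power falls from about 94% with no loss to 71% at 15% and 48% at the planned 30%. A 10-point imbalance in loss raises false rejection from 5% to about 19%. These figures are illustrative. They take the pilot IDA change for sham, zero change for every lost participant, loss unrelated to outcome and, for the 94%, no dilution in those who stop treatment. They show the effect of all missing Visit 13 data; the share due to these grounds is unknown. The change should be made while Visit 13 can still be collected.

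**What to change.** Leave the grounds for stopping study treatment unchanged and divide the section in two:

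1. **Discontinuation of study treatment**, on the grounds already listed.
2. **Withdrawal from follow-up**, limited to withdrawal of consent to follow-up or loss to contact.

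State that everyone in the first category who is not also in the second is invited to the scheduled Visit 13 for O-SCORAD, the secondary outcomes and safety, and to the economic measures as scheduled. Analyse their observed values in the FAS and ITT sets. At the analysis stage, let compliance and violations serve only to define the per-protocol set; this does not alter when treatment is stopped. If the full protocol already provides for such assessments, a sentence in this section saying so is enough.

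The cost is protocol wording and a few more assessments. Values taken off treatment will dilute the effect somewhat, as the dilution step above shows.

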### Sample size

In our previous study, the mean changes in the O-SCORAD score for 4 weeks were 9.2 ± 3.73 and 7.2 ± 3.91 in the BMA-AD and IDA-AD groups, respectively. Based on these results, we will conservatively evaluate the changes for 4 weeks in the BMA and sham devices. The number of participants required for this study was calculated as follows:$${n}_{1}=\frac{{2({Z}_{\alpha/2}+{Z}_{\beta})}^{2}{\sigma}^{2}}{{\left(\mu1-{\mu}_{2}\right)}^{2}}=64$$

The required sample size was determined to be 64 cases per group (‘experimental group’ and ‘control group’).$$N=\frac{{n}_{1}}{1-r}\cong92$$

Assuming a 30% drop out rate of participants at follow-up, we calculated the sample size to be 92 cases for each group and a total of 184 participants for both groups.

